### 6.1.1. Populations

Intent-to-treat subjects are defined as all randomized subjects who receive at least one dose of study medication and have some follow-up data. Per protocol subjects are a subset of the intent-to-treat subjects who complete the study without any major deviations from the protocol procedures. The primary efficacy analysis will be carried out for the intent-to-treat population, and the analysis will also be performed for the per protocol population. The safety analysis will be performed on the intent-to-treat population only.

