| **Investigational plan:** | Approximately 1000 subjects will be screened in order to enroll 355 subjects at approximately 30 U.S. centers in order to obtain approximately 70 evaluable subjects for the placebo, 4, 8 and 16 mg prosaptide dose arms. Approximately 18 months will be allotted for recruitment from the first to the last subject’s 1st screening visit (Visit 1). The study will be divided into a screening period, baseline period, a six week active treatment period, and a two week crossover period. Thirteen weeks will be allotted for each subject from Visit 1 until the completion of the study (Visit 8). |
| --- | --- |
| **Treatment:** | Active treatment: Subjects will be randomized to prosaptide 2, 4, 8, or 16 mg or look-alike placebo in a double blind manner until all opened drug blocks with the 5 dose groups have been used. Subsequently, subjects will be randomized to one of only three prosaptide doses (4, 8 or 16 mg) or placebo in a double-blind manner. |
| **Regimen:** | The treatment plan is as follows:  At Visit 3, subjects will be randomized to one of the prosaptide doses), or look-alike placebo in a double-blind manner.  At Visit 4, subjects will receive one of the dosing levels of drug or placebo (double-blind treatment phase).  At Visit 7, subjects will be “crossed over” with subjects who received active drug receiving placebo and subjects who received placebo receiving 4 mg of prosaptide (double-blind crossover phase). |
| **Investigational drug:** | Prosaptide is supplied for human use as a clear, colorless, odorless sterile solution in phosphate buffer containing 3% mannitol with a pH of 6.8. All dosages are packaged in 2 mL sterile glass vials with Teflon-faced stoppers and flip-off caps. |
| **Reference therapy:** | Look-alike placebo will be supplied as sterile phosphate buffered saline with 3% mannitol, pH 6.8. |

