## 3.1. Overall study design

This will be a randomized, double-blind, placebo-controlled multicenter study design using four dosing levels (2, 4, 8, and 16 mg/day) to evaluate the efficacy and safety of prosaptide for the relief of neuropathic pain associated with HIV-1. An interim analysis will be performed when 200 subjects complete 6 weeks of treatment.

Subjects will be washed out of **adjuvant pain medications** including anticonvulsants, antidepressants, topical analgesics and short-acting narcotics. Long acting opioid analgesics (maintained at a constant daily dose throughout the study) will be permitted in up to 20% of screened subjects at each study site. Subjects taking long-acting narcotics must have received a constant daily dose for at least 30 days prior to Visit 1. All subjects will receive a supply of **acetaminophen 500 mg caplets** as **rescue medication**. Subjects who have intolerable pain despite rescue medication are permitted to discontinue from the study at any time.

The double-blind phase will include a 6 week active treatment phase with subjects receiving one of the 4 dosing levels of prosaptide or placebo as illustrated in Figure 3-1.

Subjects who meet entry criteria, including a pain level of Gracely 0.74 log units averaged over the 2-week period between Visit 2 and Visit 3, and have completed written informed consent will be randomized into the study. Subjects randomized after the **two part** screening phase will complete a one week baseline period, then will receive one of four active treatment or placebo for a **42-day** double-blind treatment period. This will be followed by a **2-week** double-blind **crossover period**, during which subjects previously receiving active treatment will receive placebo injections. **The group receiving placebo during the 42-day double-blind treatment period will be crossed over to receive prosaptide 4 mg for 2 weeks,** forming a modified **cross-over** design*.* The purpose of the crossover period is to assess the duration of prosaptide response after discontinuation of treatment. In addition, it increases the number of subjects who receive active treatment, enhancing the ability to assess the magnitude of the placebo response, and the secondary outcome of early pain response. It also allows all subjects the opportunity to receive active therapy at some point during the study. Study visits will occur every 2 weeks during both double-blind periods.

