# 6. Statistical methods

## 6.1. Statistical methods

This is a double-blind, randomized, placebo controlled study with five dose groups (0, 2, 4, 8, 16 mg/per day). The primary efficacy endpoint is the change of the Gracely pain average score during Week 6 from the Week 0 baseline level (Week 0 minus Week 6 score). The primary objective is to select at least one dose group which is significantly better than the placebo with respect to this endpoint. Furthermore, the dose response relationship among these four groups will be examined.

Due to the slow enrollment, the protocol is amended to restrict further enrollment in the lowest dose arm (2 mg). It is expected that a sufficient number of subjects will have been treated at 2 mg before the amendment is fully implemented. An inferential statistical comparison between the 2 mg and placebo groups will still be carried out if there is a sufficient statistical power to detect a clinically meaningful treatment difference. Regardless, all dose groups will be used to characterize safety and dose response.

The study will be stratified with respect to SNAP (+ or -). For each stratum, a random treatment allocation rule will be utilized so that the balance among these five dose groups (four dose groups after the amendment) within each center will be maintained during the study.

It is planned that the data from all centers that participate in this protocol will be combined, so that an adequate number of subjects will be available for analysis. The results from each center will also be presented individually. In addition, it is planned that the data from both SNAP positive and SNAP negative subjects will be combined in the final analysis if there is no interaction between treatment effects and SNAP status.

The significance for all statistical tests will be reported at the p=0.05 level, and all tests will be 2-sided. Each dose group will be compared to the placebo group and a 95% confidence interval for each comparison will be provided. Because this is a phase 2 study, no adjustments for multiplicity will be made.

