### 6.1.5. Efficacy evaluation

The primary analysis will be an intent-to-treat analysis. The standard 95% confidence intervals for treatment differences between each dose and placebo groups will be constructed for the primary efficacy endpoint. Since the study is stratified with respect to the SNAP status, separate confidence intervals will be constructed for each stratum. If there is no interaction between treatment efficacy and SNAP, the two intervals will be combined across the strata to have a global confidence interval for evaluating each dose effect. If the safety profiles for the four dose groups are similar, the recommended dose will be the one with the best efficacy (largest lower bound of the confidence interval).

Similar analyses will be repeated for the secondary efficacy endpoints. For the secondary endpoint analyses, the weekly pain scores will be calculated for each subject. In order to take advantage of such repeated measurements in the analysis, a 95% confidence interval of the difference between a dose group and the placebo will be constructed at each week. These intervals will be combined using the technique by Wei and Johnson25 to obtain a single more informative confidence interval for the treatment difference over the entire study period.

Subjects with greater than 0.35-unit pain improvement on the 13-point Gracely scale at Week 6 will be classified as treatment successes. Treatment group comparisons will be carried out using the Chi-square test and Fisher’s exact test. The standard confidence interval of the difference of the weekly success rates between a dose group and placebo will be constructed. For this dichotomized response, a single interval estimate across the entire study period will be computed using the Wei and Johnson technique.

In addition, an analysis of covariance (ANCOVA) which adjusts for the differences in baseline Gracely pain scale will be conducted for both primary and secondary efficacy endpoints. Primary and secondary efficacy analyses will also be repeated adjusting for other factors that may affect the outcome. Candidate predictive factors are SNAP amplitude at baseline, type of sensory neuropathy (DSP versus ATN), CD4 counts, plasma viral load, age, body mass index (BMI), duration of disease, and background antiretroviral therapy.

Additional efficacy analyses will include per protocol analyses. The previously described statistical approach will be repeated for this population.

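### Protocol Section 6.1.1 requires completion through Visit 8 for the per protocol set, so subjects with clean Week 6 data can be removed from the Week 6 comparison for events in the crossover

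*Protocol*

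**What the plan says.** Section 6.1.1 admits to the per protocol set only those intent-to-treat subjects "who complete the study without any major deviations from the protocol procedures". It makes the primary efficacy analysis intent-to-treat and adds that "the analysis will also be performed for the per protocol population". Section 6.1.5 confirms this ("Additional efficacy analyses will include per protocol analyses") and repeats the same statistical approach without redefining the set.

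The synopsis ties completion to the last visit: each subject is allotted thirteen weeks from Visit 1 "until the completion of the study (Visit 8"). Section 3.4.3 likewise sets the goal as follow-up through Visit 8.

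The endpoint comes earlier. Section 6.1 states: "The primary efficacy endpoint is the change of the Gracely pain average score during Week 6 from the Week 0 baseline level". Section 3.4.2 labels Visit 7 the end of the active treatment phase, and Section 3.3.4 describes Week 6 as the week before Visit 7. Section 3.1 then describes a two-week double-blind crossover "during which subjects previously receiving active treatment will receive placebo injections", while the placebo group moves to prosaptide 4 mg.

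**The concern.** Membership of the per protocol set depends on what happens in the two weeks after the Week 6 endpoint has been measured, and the treatment given in those weeks is determined by the randomised arm.

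Several rules can remove a subject in that window, because none stops at Visit 7:

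- discontinuation for treatment failure, which is a pain-driven request to leave (Section 3.4.3);
- the missed-dose rule, which applies to any two-week interval (Sections 3.3.1 and 3.4.3);
- exclusion from the per protocol analysis for a change of long-acting opiate or dideoxynucleoside regimen after Visit 3 (Sections 3.3.4 and 3.4.3).

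At the least, usable Week 6 data are left out of a planned repeat of the primary analysis. If crossover loss is also related to the Week 6 change, and differently so by arm, the per protocol difference from placebo could be biased by events that cannot have influenced the measurement.

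**Working it through.** **1. Inputs from the protocol.** Section 6.3 gives a design difference of 0.17, an SD of change of 0.35, a placebo response of about 0.17, 70 evaluable per group, and at least 80% power at two-sided 0.05. Section 3 (Investigational plan) gives 10% dropout, with 280 completers balanced over four groups. Section 2.4 defines treatment success as an improvement of at least 0.35.

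**2. The protocol's own figures.**

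- Power with 70 per group, normal approximation: 82.0% (81.4% with the t distribution), which meets the stated 80%.
- Half-width of the 95% interval: 1.96 × 0.35 × √(2/70) = 0.116, stated as 0.12.
- Enrolment: 280/0.9 + 45 = 356, against 355 stated.

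These reproduce, so the inputs are usable.

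**3. Assumptions not in the protocol.** It gives no crossover loss rate. Take an active arm with mean improvement 0.17 + 0.17 = 0.34, SD 0.35 and normally distributed changes. Suppose 5% of non-successes and 10% of successes are lost between Visits 7 and 8, with no selective loss on placebo.

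**4. Split at 0.35.** z = (0.35 − 0.34)/0.35 = 0.0286, with normal density 0.3988.

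- Success share: 0.4886. Non-success share: 0.5114.
- Mean in successes: 0.34 + 0.35 × 0.3988/0.4886 = 0.6257.
- Mean in non-successes: 0.34 − 0.35 × 0.3988/0.5114 = 0.0671.

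**5. Re-weight after loss.**

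- Retained: 0.4886 × 0.90 + 0.5114 × 0.95 = 0.4397 + 0.4858 = 0.9256, so the loss is 7.4%, about 5 of 70.
- Retained mean: (0.4397 × 0.6257 + 0.4858 × 0.0671)/0.9256 = 0.3325.
- Shift: 0.3325 − 0.34 = −0.0075, about 0.008 in size; 0.0075/0.17 = 4%.

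**6. Reverse the pattern.** With 5% of successes and 10% of non-successes lost, the retained mean is (0.4886 × 0.95 × 0.6257 + 0.5114 × 0.90 × 0.0671)/0.9244 = 0.3476, a shift of +0.008. The sign depends entirely on who leaves.

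**7. Check against the 10% allowance.** Overall active-arm loss in the crossover alone, with 5% loss in non-successes:

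| Loss in successes | Active-arm loss | Shift in mean |
|---|---|---|
| 10% | 7.4% | about 0.008 |
| 15% | 9.9% | about 0.016 |
| 25% | 14.8% | about 0.033 |

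Only the first row leaves room for dropout in Weeks 1 to 6: 1 − 0.90/0.9256 = 2.8%. The second uses practically the whole-study allowance, and the third exceeds it.

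**8. A second model.** Let the log-odds of crossover loss in one arm change by 1 per SD of the Week 6 change, with random loss in the other arm. At 2% and 5% loss the shift is 0.007 and 0.016. At 10% it is 0.032, but that again spends the whole allowance in two weeks. If loss is unrelated to the Week 6 change, the shift is 0.

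**The case against.** The strongest reply is that little rests on this set. Section 6.1.5 makes the primary analysis intent-to-treat and attaches the dose recommendation to it; the per protocol work is additional. A subject who leaves during the crossover keeps the Week 6 value in the primary analysis. A reader might infer that the primary result or the dose choice is compromised. The documents do not support that.

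A reader might also infer a definite direction: active-arm responders lose drug, their pain returns, they leave, and the per protocol effect is understated. The protocol does not establish this. The crossover is double-blind, rescue medication is dispensed at Visit 7, and how long any effect lasts after stopping is the question the crossover is meant to answer (Section 3.1). Nor can shifts of 9% or 19% of the design difference be relied on: they come from the 15% and 25% rows above, which use up or exceed the protocol's own dropout allowance.

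Two further points stand in part. Any per protocol set selects on post-randomisation events, so a Visit 7 cut-off removes only the two-week increment. And the meaning of a major deviation, including the window in which it counts, may be settled in a statistical analysis plan that is not shown. The completion requirement is different: the protocol states it, places completion at Visit 8, and nowhere restores an earlier cut-off. Where a summary is meant to cover only the six treatment weeks, the protocol says so, as for drug exposure in Section 6.1.3.

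**Conclusion.** The point holds as a minor defect in a stated rule. As written, Section 6.1.1 removes subjects with complete, deviation-free Week 6 data from the per protocol Week 6 comparison because of later events under arm-dependent treatment. That discards valid data for no analytic gain and could bias a supporting analysis, in a direction that cannot be known from the protocol.

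The illustrative size is about 0.008 in the active-arm mean, roughly one-fifteenth of the 0.12 half-width. It rests on an assumed loss of 10% in successes and 5% in non-successes, normally distributed changes and no selective loss on placebo. The second model gives 0.007 to 0.016 for 2% to 5% loss. Bias arises only if crossover loss is related to the Week 6 change.

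**What to change.** In Section 6.1.1, define the per protocol set for the Week 1 to Week 6 efficacy analyses as intent-to-treat subjects who complete the 6-week double-blind treatment period (through Visit 7) with no major deviation up to Visit 7. Require completion through Visit 8 only for the crossover summaries in Section 6.1 and at the end of Section 6.1.5. The per protocol exclusions mentioned in Sections 3.3.4 and 3.4.3 should be read with the same cut-off for the Week 1 to Week 6 analyses.

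This costs one sentence and a cross-reference. It changes no visit, treatment, discontinuation rule or sample size, and the per protocol set can only stay the same or grow. The crossover-related selection becomes zero; selection from events in Weeks 1 to 6 remains, as in any per protocol set.

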#### Study drug administration

After the two phase screening procedures (see Table 3-1 under Section 3.4) and the one week baseline period have been completed, the subject will be instructed in self-administration of subcutaneous injections. The **initial dose** of study drug will be **self-administered** by the study **subject** under the **observation of site personnel**. All subjects should be observed for adverse reactions for at least 30 minutes following the initial dose of study drug. All subsequent doses will be administered at 24-hour intervals for a period of 6 weeks. If a dose is **missed by more than 12 hours, it should not be given**. If the subject **misses more than 4 non-consecutive or 3 consecutive doses of study drug in a 2-week interval, the subject should be discontinued from the study due to noncompliance**.

Subjects at designated centers will also have doses administered in clinic at Visits 6 and 7 so that accurately timed samples for PK analysis can be collected. Study drug from the previous supply, not the new box should be administered at these visits. See Section 3.8: Drug levels and pharmacokinetic assessments for details.

See Appendix 3 (Study drug administration instructions) for details of the study drug administration procedure.

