#### Visits 5 and 6—Active treatment visits

Visits 5 and 6 should occur **14 ±3** days from the previous study visit. Visits 5 and 6 procedures will include:

- vital signs
- evaluation of adverse events
- safety laboratory tests
- urinalysis
- review of concomitant medications
- review of electronic diary understanding and compliance
- McGill pain questionnaire
- administer study drug in clinic (designated PK centers at Visit 6 only)
- blood collection for PK analysis (selected sites at Visit 6 only)
- rescue drug accountability
- dispense rescue medication
- study drug accountability
- dispense study drug and administration supplies (needles/syringes, alcohol wipes, sharps containers)

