#### Criteria for treatment discontinuation

Subjects can be discontinued for any of the following reasons:

1. adverse event
2. consent withdrawn
3. lost to follow up
4. non-compliance (defined by investigator judgment as significant risk of failing to comply with the provisions of the protocol that causes harm to the subject or seriously interferes with the validity of the study results)
5. protocol violation
6. administrative reason (at the discretion of the clinical investigator or sponsor)
7. treatment failure (defined as subject request to leave study due to the need for disallowed pain medication)

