## Safety assessments

Safety assessments will consist of monitoring and recording all adverse events and serious adverse events, the regular monitoring of safety laboratories, regular measurement of vital signs, and the performance of physical and neurological examinations. In addition, prosaptide serum antibodies and HIV-1 RNA will be measured, and nerve conduction studies, 12-lead EKGs, and the Karnofsky performance score completed. All adverse events must be recorded beginning at the time of informed consent, whether or not the subject has actually received study drug. Additional information with regard to safety assessments and recorded AEs is found under Sections 3.7.1-3.7.3.

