#### Defining treatment-emergent AEs including SAEs

A treatment-emergent adverse event is ANY event that emerges during treatment, having been absent during pretreatment, or worsens relative to the pretreatment state. For the purposes of this study, treatment-emergent adverse events will be defined as those events occurring after the first dose of study drug at **Visit 4**.

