### 6.1.6. Safety evaluation

The assessment of safety will be based mainly on the frequency of adverse events and on the number of laboratory values that fall outside of pre-determined ranges. The safety measures will also include vital signs, physical examination, neurological examination, HIV-1 RNA, EKG, Karnofsky performance score, nerve conduction studies and prosaptide serum antibodies.

Adverse events will be summarized by presenting, for each treatment group, the number and percentage of subjects having any adverse event, having an adverse event in each body system and having each individual adverse event. Any other information collected (i.e. severity or relatedness to study medication) will be listed as appropriate.

Laboratory data will be summarized by presenting shift tables using extended normal ranges (baseline to most extreme post-baseline value), by presenting summary statistics of raw data and change from baseline values (means, medians, standard deviations, ranges) and by the flagging of notable values (as defined in section 7.1) in data listings. Two (or more)-way frequency tables of changes in laboratory test results in terms of normal ranges at the follow-up visits versus baseline by treatment group, as well as changes in absolute values from baseline will be examined for treatment differences. Change from baseline of plasma HIV-1 RNA levels by treatment group will be specifically evaluated.

Data from other tests (i.e. electrocardiogram or vital signs) will be listed, notable values will be flagged, and any other information collected will be listed as appropriate. Any statistical tests performed, such as the Chi-square test and the t-test, to explore the data will be used only to highlight any interesting comparisons that may warrant further consideration.

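### The safety analysis is confined to an intent-to-treat set that requires follow-up data, so a dosed subject judged to have none is left out of the safety tables

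*Protocol*

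**What the plan says.** Two sentences in Protocol Section 6.1.1 (Populations) settle the matter. The first defines the set: "Intent-to-treat subjects are defined as all randomized subjects who receive at least one dose of study medication and have some follow-up data". The second applies it to safety: "The safety analysis will be performed on the intent-to-treat population only". The protocol does not define what counts as follow-up data, and it names no other safety population.

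Other sections treat exposure, not later data, as the starting point for safety:

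- Section 3.7.1: "treatment-emergent adverse events will be defined as those events occurring after the first dose of study drug at" Visit 4. No follow-up condition is attached.
- Section 3.6: "All adverse events must be recorded beginning at the time of informed consent, whether or not the subject has actually received study drug".
- Section 3.3.1 (Study drug administration): "All subjects should be observed for adverse reactions for at least 30 minutes following the initial dose of study drug".
- Section 6.1.6: the summary gives, for each treatment group, "the number and percentage of subjects having any adverse event", so a denominator is needed.

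**The concern.** Membership of the safety set depends partly on what happens after dosing. A subject can be injected at Visit 4, be exposed to study drug, and still not be counted if nothing later is judged to be follow-up data. The window for this is real. Under Section 3.4.2 the next scheduled visit, Visit 5, falls 14 ±3 days after Visit 4, and Section 3.4.3 lists withdrawn consent and "lost to follow up" among the reasons for discontinuation.

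At stake is whether the adverse event percentages describe everyone who was exposed. They feed a decision: Section 6.1.5 bases the recommended dose on efficacy provided that the safety profiles of the dose groups are similar. A subject who disappears straight after a first injection may have done so for reasons related to that injection, so the exclusion need not be neutral between arms.

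**Working it through.** **Inputs**

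- Total enrolment 355, of whom 45 in the 2 mg group (Section 6.3).
- 70 evaluable subjects in each of the other four groups (Section 6.3), with 10% dropout (Section 3).
- Number of dosed subjects without follow-up data: not stated. Taken here, as an assumption, as k = 1 to 4 per arm.

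**The plan's own figures.** The protocol gives no number for the safety set, so only the arm size can be reproduced. From total enrolment, (355 − 45)/4 = 77.5 per arm; from evaluable subjects, 70/0.9 = 77.8. In total, 280/0.9 + 45 = 356, against 355 stated. I use n = 78 for the placebo, 4, 8 and 16 mg arms and n = 45 for 2 mg. These are randomised numbers. Dosing starts a week after randomisation, so the number dosed may be a little lower and each subject worth slightly more.

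**Effect of one excluded subject.** Let x of n dosed subjects have a recorded event, with p = x/n.

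- The excluded subject had a recorded event, so numerator and denominator both fall by one: x/n − (x − 1)/(n − 1) = (1 − p)/(n − 1). This is the fall in the rate.
- The excluded subject had none, so only the denominator falls: x/(n − 1) − x/n = p/(n − 1). This is a rise.

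The fall is below 1/(n − 1), which is 1/77 = 1.3 points in an arm of 78 and 1/44 = 2.3 points in an arm of 45. The largest value actually reached is when the excluded case is the only one: 1/78 = 1.3 and 1/45 = 2.2 points. It shrinks as the event becomes common: at p = 50% and n = 78 it is 0.5/77 = 0.65 points.

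**Several excluded subjects**

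| Arm | Excluded (k) | Recorded events | Rate as written | Rate, all dosed | Difference (points) |
|---|---|---|---|---|---|
| 78 | 1 | only in the excluded | 0/77 = 0% | 1/78 = 1.3% | −1.3 |
| 78 | 4 | only in the excluded | 0/74 = 0% | 4/78 = 5.1% | −5.1 |
| 78 | 3 | 39 in all, 3 in the excluded | 36/75 = 48.0% | 39/78 = 50.0% | −2.0 |
| 78 | 4 | 2, none in the excluded | 2/74 = 2.7% | 2/78 = 2.6% | +0.1 |
| 45 | 1 | only in the excluded | 0/44 = 0% | 1/45 = 2.2% | −2.2 |
| 45 | 4 | only in the excluded | 0/41 = 0% | 4/45 = 8.9% | −8.9 |
| 45 | 4 | 2, none in the excluded | 2/41 = 4.9% | 2/45 = 4.4% | +0.4 |

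The rows in which every excluded subject had the event and no retained subject did are the extreme, not a forecast.

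**The case against.** The strongest reply is that hardly anyone would be excluded. The first dose is taken in clinic with at least 30 minutes of observation; adverse events are recorded for everyone; the diary uploads nightly (Section 3.5.1); a discontinuation visit is required of anyone who stops after the first dose (Section 3.4.3); and serious events are reportable until 30 days after treatment ends (Section 3.7.3). Any of these could be read as follow-up data. This stands as a limit on size. It does not remove the rule: the condition is undefined, a lost subject cannot be made to attend a visit, and entry to the safety set should not turn on a reading chosen later.

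A second reply is that the word *only* means merely that safety is not repeated in the per-protocol set, because the preceding sentence runs efficacy on both sets. That may be the intention. Even so, the set that remains carries the follow-up condition, and no all-dosed set stands beside it. A statistical analysis plan, not available here, could define one, but it would then contradict Section 6.1.1.

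A reader might go further and infer three things that the protocol does not support:

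- *That event rates are biased downwards.* This needs subjects whose event was recorded but who still count as having no follow-up data, and the protocol nowhere says that a recorded post-dose event would fail the condition. A subject with no recorded event only shrinks the denominator, which raises the rate.
- *That the condition concerns efficacy data.* The text does not say which data count.
- *That safety is tabulated by randomised arm, so that a subject given the wrong kit is counted under a drug not received.* Section 6.1.6 speaks only of treatment groups.

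Nor is anything lost from collection or oversight: adverse events are recorded for every subject, and serious-event summaries go to the monitoring board as they occur (Section 6.2).

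**Conclusion.** The point holds as a defect in the stated analysis set. Section 6.1.1 makes the safety tables conditional on data obtained after dosing, while the protocol's definition of treatment-emergent events asks only for a first dose. The effect is probably small, and its sign is not fixed: a fall of at most about 1.3 points per excluded case in an arm of about 78 (about 2.3 in the 2 mg arm) if the case had a recorded event, and a slight rise if not. These figures rest on planned arm sizes and on an assumed number of exclusions, because the protocol gives none. They do not show that the dose recommendation would be distorted. The change is worth making because the all-dosed set is the plainly better choice and costs almost nothing.

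**What to change.** In Section 6.1.1, define a safety population: all subjects who receive at least one dose of study medication, with or without follow-up data. Replace the sentence "The safety analysis will be performed on the intent-to-treat population only" with one stating that the safety analysis uses this population. It would also help to say what counts as follow-up data for the intent-to-treat set, which the efficacy analysis would still use.

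The cost is one definition and one changed sentence, carried into the statistical analysis plan. No visit, measurement or subject is added, and sample size and power are untouched, since they rest on evaluable subjects for the pain endpoint. The change does not recover events that were never recorded; it ensures that every exposed subject, and every event recorded in one, is counted.
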